**Table 1. Risk/benefit monitoring and measures**

| Risk factors:            | Monitoring/measures:                                                                                                                                                                                                                                    |
|---------------------------------|----------------------------------------------------------------------------------------------------------------------------------------------------------------------------------------------------------------------------------------------------------------|
| Diarea, nausea, vomiting | Information about prophylactic procedures and treatment at study start
First follow-up after 4 weeks
Weight measures every follow-up                                                                                                                     |
| Infections               | Information sent to the GP at study start                                                                                                                                                                                                                      |
| Psychiatric symptoms     | GHQ 28 at every visit
Phone calls/visits every 4 weeks
Contact study personnel by phone or e-mail 24 hours
Known depression is an exclusion criterium
Information sent to the GP at study start
Avoid concomitant medication that increase risk |
| Benefits:                | Monitoring/measures:                                                                                                                                                                                                                                    |
| Reduced pain                    | GELP score, PGA, PtGA                                                                                                                                                                                                                                          |
| Reduced inflammation            | GELP score, photos                                                                                                                                                                                                                                             |
| Reduced sexual distress         | DFDS score, PtGA                                                                                                                                                                                                                                               |
| Improved quality of life        | QOL score, PtGA                                                                                                                                                                                                                                                |

## 2 STUDY OBJECTIVES AND RELATED ENDPOINTS

The main objective of this trial is to assess the efficacy of apremilast in the treatment of GELP in women.

Table 2 describes the relation between objectives and endpoint.

**Table 2**

|                    | Objectives                                                                                                                    | Endpoints                                                                                                                                                                                                                                                                                                                                                                                                                                                                                                                                                                                                                                                                                                                                                                                                                                                                                                                                                                                                            |
|--------------------|-------------------------------------------------------------------------------------------------------------------------------|----------------------------------------------------------------------------------------------------------------------------------------------------------------------------------------------------------------------------------------------------------------------------------------------------------------------------------------------------------------------------------------------------------------------------------------------------------------------------------------------------------------------------------------------------------------------------------------------------------------------------------------------------------------------------------------------------------------------------------------------------------------------------------------------------------------------------------------------------------------------------------------------------------------------------------------------------------------------------------------------------------------------|
| Primary     | To assess the effect of apremilast treatment in women with GELP                                                               | 
Primary
 
 
• Mean GELP score at week 24 in apremilast-treated patients versus placebo-treated patients
 
 
Secondary
 
 
• Mean GELP score improvement from week 0 to week 24 in all patients
 
• Weekly use of topical steroid, collected from patient diary
 
• Weekly VAS pain score, collected from patient diary
 
• Number of patients with GELP score improvement at week 16 and 24
 
• Separate GELP score assessments: Area of involvement (in cm^2), number of erosions, erythema, striae and pain (VAS) at week 4, 16 and 24
 
• Physician Global Assessment (PGA) and Patient Global Assessment (PtGA) scores at week 0, 16 and 24
 
 
Exploratory
 
 
• Description of extragenital lichen planus at week 0, 16 and 24
 
• Clinical photos taken at week 0 and week 24
 
 |
| Secondary   | To assess quality of life in women with GELP before and during apremilast treatment                                           | Selected QoL measures (DLQI, GHQ-28) at week 0, 16 and 24                                                                                                                                                                                                                                                                                                                                                                                                                                                                                                                                                                                                                                                                                                                                                                                                                                                                                                                                                            |
|                    | To assess sexual function in women with GELP before and during apremilast treatment                                           | Sexual function assessments (FSDS-R) at week 0, 16 and 24                                                                                                                                                                                                                                                                                                                                                                                                                                                                                                                                                                                                                                                                                                                                                                                                                                                                                                                                                            |
| Exploratory | To describe immune histochemical changes and expression of selected cytokines in GELP lesions after treatment with apremilast | 
 
• Description of immune histochemical changes and expression of selected cytokines before and after apremilast therapy, assessed in vulvar or vaginal biopsies at week 0 and 24
 
                                                                                                                                                                                                                                                                                                                                                                                                                                                                                                                                                                                                                                                                                                                                                                                    |

## **2.1 Primary Endpoint**

1. Mean GELP score at week 24 in apremilast-treated patients versus placebo-treated patients

## **2.2 Secondary Endpoints**

2. Mean GELP score improvement from week 0 to week 24 in all patients
3. Weekly use of topical steroid, collected from patient diary
4. Weekly VAS pain score, collected from patient diary
5. Number of patients with GELP score improvement at week 16 and 24
6. Separate GELP score assessments: Area of involvement (in cm^2), number of erosions, erythema, striae and pain (VAS) at week 4, 16 and 24
7. Physician Global Assessment (PGA) and Patient Global Assessment (PtGA) scores at week 0, 16 and 24
8. Selected QoL measures (DLQI, GHQ-28) at week 0, 16 and 24
9. Sexual function assessments (FSDS-R) at week 0, 16 and 24

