**Main Exclusion Criteria**

- Patients receiving other systemic immune modulating therapy

- Concomitant use of strong CYP3A4 enzyme inducers
- Inadequate birth control, pregnancy and/or breast-feeding
- Depression and suicidal ideation
- Patients with severe renal impairment
- Patients with active tuberculosis, serious infections or cancer
- Unexplained and clinically significant weight loss in underweight patients
- Hypersensitivity to the active substance(s) or to any of the excipients
- Hereditary problems of galactose intolerance, lactase deficiency or glucose-galactose malabsorption
- Participating in another trial that might affect the current study or there should be minimum 90 days between participation in another intervention trial

**Sample Size:** 42 patients

**Efficacy Assessments:** GELP score, FSDS, DLQI, GHQ-28, PGA, PtGA

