## **3 OVERALL STUDY DESIGN**

There are very few controlled studies on treatment of GELP in women. The Cochrane Database systematic review on treatment of erosive lichen planus affecting mucosal sites(9) concludes that more RCTs on a larger scale are needed in the oral and genital ELP populations and suggest that future studies should have standardized outcome variables that are clinically important to affected individuals.

This is a phase 2, single-center, randomized, placebo-controlled, double-blind, parallel-group study.

An equal number of participants are randomized to apremilast- or placebo treatment arms. Based on experience from previous studies on apremilast used for other indications, effect is usually achieved within 3-4 months,(29) with some expected additional effect for another two months.

**Screening** will be performed no more than 90 days prior to baseline visit. Patients will receive information on participation at screening visit.

Patients who qualify for participation according to inclusion criteria and who have signed the informed consent form will be included at baseline visit (day 0). They will be randomized at inclusion to receive either study medication (apremilast) or placebo. Screening and baseline visit may be on the same day, but preferably patients will have at least 24 hours between screening and baseline to allow adequate time for patient information/ informed consent.

**Randomization** will be performed in the electronic data capture system Viedoc which includes a randomization module and both patients and clinicians will be blinded for the allocation. The study is double-blinded for the randomization throughout the treatment period and until end of trial.

Following randomization, 21 patients will receive study medication (oral apremilast) and 21 patients will receive oral placebo. Initial standard titration of dose day 1-6 is followed by standard dose of 30 mg apremilast b.i.d. or placebo b.i.d for a total period of 24 weeks. Tablet blister cards are identical in appearance in both groups.

|                            |                                                                                                                                                                                                                                |

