### 4.3 Exclusion Criteria

Patients will be excluded from the study if they meet any of the following criteria:

- Patients receiving other systemic immune modulating therapy. Immune modulating therapy other than the study drug is prohibited during the study. Subjects who have been taking the following medications must adhere to the following minimum washout periods:
  - Four weeks prior to the day of inclusion for non-biologic systemic immunosuppressive agents
  - Twelve weeks prior to the day of inclusion for adalimumab, infliximab, etanercept and similar agents
  - Twelve months prior to the day of inclusion for rituximab.
- Concomitant use of strong CYP3A4 enzyme inducers. Apremilast exposure is decreased when administered concomitantly with strong inducers of CYP3A4 and may result in reduced clinical response. The use of strong CYP3A4 enzyme inducers (e.g. rifampicin, phenobarbital, carbamazepine, phenytoin and St. John's Wort) with apremilast is not recommended.(29)
- Inadequate birth control, pregnancy and/or breast-feeding
- Depression and suicidal ideation (GHQ-28 score more than 7/28)
- Patients with severe renal impairment (creatinine clearance of less than 30mL per minute) as described in SmPC
- Patients with active tuberculosis, serious infections or cancer
- Unexplained and clinically significant weight loss in underweight patients
- Hypersensitivity to the active substance or to any of the excipients (listed in SmPC)
- Hereditary problems of galactose intolerance, lactase deficiency or glucose-galactose malabsorption
- Participating in another trial that might affect the current study or there should be minimum 90 days between participation in another intervention trial

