## 7.2 Safety and Tolerability Assessments

Safety will be monitored through the assessments described below as well as registration of AEs at each visit. Significant findings that are present prior to the signing of informed consent will be included in the relevant medical history/ current medical condition page of the CRF. For details on AE collection and reporting, see section 8.

For the assessment schedule, see flow chart in section 6.1, and table 1.

**Physical examination** will include

- Inspection of the genital area, the cavum oris and, if relevant, other affected skin areas.
- Blood pressure.
- Cardiac and pulmonary auscultation.

**Body weight** will be measured in indoor clothing, without shoes.

**GHQ-28** will serve as a screening device to assist the assessment of negative psychological effects of study medication.

**Pregnancy tests** (in WOCBP) will be performed monthly, at study visits or by the patient at home. The result will be reported to study personnel monthly.

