#### **Quality of life questionnaires:**

Three validated QoL questionnaires will be used. To be able to compare the results with studies in other vulvar and/or mucosal inflammatory diseases, we have chosen questionnaires that have been used in previous GELP QoL studies(31, 32):

*DLQI – Dermatological Life Quality Index*

*FSDS – Female Sexual Distress Scale*

*GHQ28 – General Health Questionnaire*

*DLQI* is a widely used questionnaire aiming to measure the impact of skin disease on adult patients' quality of life. The *DLQI* consists of 10 items covering six basic topics: symptoms and feelings, daily activities, leisure, work or school, personal relationships, and treatment.(33)

*FSDS* is a standardized 13-item scale for assessment of sexually related personal distress in women. It may serve as a screening tool to identify women with high and low sexual function.(34)

*GHQ28* is a screening device for identifying minor psychiatric disorders. It is a 28-item scaled version assessing somatic symptoms, anxiety and insomnia, social dysfunction and severe depression.(35)

The results will be compared with the results from studies in patients with genital psoriasis, lichen sclerosis and vulvar dermatitis.

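### The GHQ-28 entry cap of 7/28 limits what this quality-of-life endpoint can show and biases the planned comparison of its level with other disease series

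*Protocol*

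**What the plan says.** The protocol gives GHQ-28 four roles.

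- **Entry criterion.** Section 4.3 opens with "Patients will be excluded from the study if they meet any of the following criteria" and lists "Depression and suicidal ideation (GHQ-28 score more than 7/28". The cut-off applies to the total score. Section 7.3 describes the questionnaire thus: "It is a 28-item scaled version assessing somatic symptoms, anxiety and insomnia, social dysfunction and severe depression". The cap therefore restricts the whole instrument, not only its depression items. The synopsis gives the same exclusion without the cut-off.
- **Efficacy.** Section 2.2, Table 2 and the synopsis carry the secondary endpoint "Selected QoL measures (DLQI, GHQ-28) at week 0, 16 and 24". The synopsis line on efficacy assessments reads "GELP score, FSDS, DLQI, GHQ-28, PGA, PtGA". In Table 2, DLQI and GHQ-28 are the only measures given for the quality-of-life objective.
- **Safety.** Section 7.2 says GHQ-28 "will serve as a screening device to assist the assessment of negative psychological effects of study medication".
- **Outside comparison.** Section 7.3, on the questionnaires, says "The results will be compared with the results from studies in patients with genital psoriasis, lichen sclerosis and vulvar dermatitis". GHQ-28 is not exempted.

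On timing, Table 3 places the eligibility assessment at screening only, and screening "will be performed no more than 90 days prior to baseline visit". GHQ-28 is measured at screening and again at baseline, and no second check against the limit is stated. No section mentions the restricted range.

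**The concern.** A variable that decides who enters has a distribution partly made by the entry rule. Two uses of GHQ-28 suffer from this.

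First, entrants qualify in the lowest quarter of the scale. A treatment that relieves symptoms has few points to remove, while worsening has most of the scale open to it. That suits a safety screen but not an efficacy measure. A null GHQ-28 result could be taken as evidence against a quality-of-life benefit that the measure had little chance to show.

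Second, the outside comparison is one of levels. If the other series did not cap GHQ-28, the GELP sample will look psychologically healthier because of how it was selected. Section 1.4 justifies the questionnaires by the lack of larger quality-of-life studies in similar patients, so a burden figure that is too low would undercut one of the study's own purposes.

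**Working it through.** **The plan's own figure.** The protocol gives no number for GHQ-28 as an endpoint. Its only sample-size figure concerns the GELP score (section 10.1): difference 4, SDs 4.5 and 4.2, two-sided 5%, 80% power. The pooled SD is √((4.5² + 4.2²)/2) = 4.353. The normal approximation gives 19 per group. The exact t calculation gives 19.6, so 20 per group with 80.8% power. The stated 20 is reproduced. With 20 per group, the standardised difference detectable with 80% power is 0.909.

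**What follows from the text alone.** A qualifying score lies between 0 and 7.

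- Largest possible fall: 7 points; 7/28 = 25% of the scale.
- Possible rise: 28 − 7 = 21 to 28 − 0 = 28 points.
- The average room to fall is the mean qualifying score. It is below 7 unless every woman scores exactly 7, and would be 3.5 if scores were uniform on 0 to 7.
- For any distribution with scores above 7, the mean of those at or below 7 is lower than the mean of all. The direction of the selection effect at screening is therefore certain.

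**Illustration of size (assumed, not in the documents).** Take a beta-binomial score on 0–28 with the unselected mean and SD shown, cut at 7. Gap = unselected mean − entrant mean.

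| Unselected mean, SD | Excluded | Entrant mean | Entrant SD | Gap |
|---|---|---|---|---|
| 3, 4 | 13% | 1.73 | 2.05 | 1.27 |
| 3, 6 | 15% | 0.78 | 1.62 | 2.22 |
| 5, 4 | 24% | 3.19 | 2.16 | 1.81 |
| 5, 6 | 26% | 1.95 | 2.18 | 3.05 |
| 7, 4 | 41% | 4.28 | 1.96 | 2.72 |
| 7, 6 | 39% | 2.97 | 2.28 | 4.03 |
| 9, 4 | 62% | 5.04 | 1.70 | 3.96 |
| 9, 6 | 54% | 3.77 | 2.19 | 5.23 |

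**Allowing for drift after screening.** Scores selected for being low tend to rise at the next measurement. With SD 6 and an assumed correlation of 0.6 or 0.8 between screening and a later visit:

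| Unselected mean | Correlation | Later mean | Later SD | Later score above 7 | Gap |
|---|---|---|---|---|---|
| 5 | 0.6 | 3.39 | 4.61 | 16% | 1.61 |
| 5 | 0.8 | 2.73 | 3.70 | 11% | 2.27 |
| 7 | 0.6 | 4.72 | 4.58 | 23% | 2.28 |
| 7 | 0.8 | 3.88 | 3.68 | 16% | 3.12 |

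Drift narrows the gap but does not close it.

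**Sensitivity to benefit.** Detectable difference = 0.909 × SD. In the four drift scenarios it is 3.4 to 4.2 points, which is 86% to 124% of the later mean. Near-complete removal of symptoms would be needed, and above 100% even that would not suffice. Without a cap, the same sum gives 0.909 × 6 = 5.45 points: 5.45/5 = 109% and 5.45/7 = 78%. Adjusting for baseline would lower all these figures somewhat (by a factor √0.75 = 0.87 if the correlation were 0.5). As a share of the mean, then, most of the low power comes from having 20 women per arm on a skewed scale, and the cap adds to it only modestly. What the cap firmly removes is the number of points available to improve.

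**The case against.** The case for leaving the plan alone has real substance.

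- The cap acts at screening. The week 0 value that enters the analysis is taken up to 90 days later and is not bounded at 7. This stands: the endpoint is not strictly truncated.
- The between-arm comparison is randomised and adjusted for baseline (section 10.5.4), so it is unbiased. Section 10.5.1 makes every non-primary efficacy analysis supportive or exploratory. DLQI and FSDS-R are not directly capped. All of this stands.
- Only the exclusion criterion gives a denominator of 28. The endpoint sections state no scoring rule, so applying the 7-point limit to the outcome assumes the same total is used.
- The outside comparison is one sentence with no analysis attached, and how the comparator patients were selected is not given. This limits what can be said about size. It does not rescue an unqualified comparison.

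A reader might go further and infer that GHQ-28 has almost no room to improve, that it cannot be compared with any other series, or that it should be struck from the endpoints. The documents support none of these. If entrants cluster near 7, the loss of room is mild. A comparison restricted to patients at or below the same limit remains possible. The first patient was enrolled on 24.09.2019, and dropping a prespecified endpoint after that could itself look like selective reporting. Listing GHQ-28 under both efficacy and safety is also not a contradiction.

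**Conclusion.** The point holds as a limit on interpretation and as a bias in one planned comparison; it is not a flaw in the randomised analysis. The firm figure is a maximum improvement of 7 of 28 points (25%) from the qualifying score, assuming the outcome uses the same total. That limits sensitivity to benefit and leaves the safety use intact.

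The outside comparison is the part that needs changing. Against series without such a cap, a plain comparison of GHQ-28 levels would understate the psychological burden of GELP. The direction follows from the entry rule. The size, 1.3 to 5.2 points at screening or 1.6 to 3.1 with drift in the scenarios shown, rests wholly on assumed distributions and correlations.

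The protocol does not say that a null GHQ-28 result will be read as no effect on quality of life. That is a risk to guard against, not a stated plan. Overall this is a cheap improvement.

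**What to change.** 1. In section 7.3, limit the outside comparison to DLQI and FSDS-R. Alternatively, compare GHQ-28 only with patients at or below the same limit, using the screening score, which is the one the rule acts on.
2. Keep GHQ-28 as a prespecified between-arm outcome, but name DLQI as the main quality-of-life efficacy measure. Report GHQ-28 by arm mainly as a safety or descriptive measure, for example the number of women above 7 and the change from baseline.
3. State the entry restriction wherever GHQ-28 is reported, and say that a null result on it is not evidence of no effect on quality of life.

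The exclusion rule itself is a clinical matter and is not questioned here.

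The cost is small: no new data, and no change to the primary endpoint or sample size. One outside comparison is dropped or restricted, and the restricted form depends on other series reporting scores in a way that allows it. The change to section 7.3 can go into an amendment under section 11.3, and the reporting rules into the statistical analysis plan before database lock (section 10.4).
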